### Randomization

2.6

Eligible participants will be randomized into the experimental group or control group using a complete randomization scheme generated in advance. Specifically, the randomization scheme will be generated in the computer program Stata/SE15.1 by a member of the research staff ([name]) who is not involved in recruitment or intervention and is not the principal investigator. The assignment of participants will be hidden using sequentially numbered-sealed e-mails, which will only be opened by the researchers after the informed consent form is signed. The study grouping will be revealed at the same time to both the patient and researchers.

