### Interventions

2.7

The standard treatment for insomnia will be BBT-I,^[14]^ including sleep restriction, stimulation control, and sleep hygiene education.^[9,53–55]^ The implementation of sleep restriction and stimulation control will be guided by trained community physicians in the outpatient clinics. The corresponding bedtime, wake-up time, and other related recommendations for behavioral treatment will be given to the participants according to their sleep conditions and will be adjusted during the follow-up based on the 1-week sleep diary. Sleep hygiene education will be conducted in the form of health lectures and online free consultations. Related video resources will also be distributed to allow participants to partake in further study to better understand their condition. Although complete CBT-I may be the best treatment option, BBT-I is a standard treatment that can be conducted in primary medical institutions in the Chinese community because of its simple and easy implementation.

Considering the various non-adherence issues that occur in the implementation of BBT-I, we will schedule TCMET in BBT-I to improve patient's behavioral adherence in the experimental group. TCMET include *Wuqinxi* qigong exercise, Chinese medicine massage, and herbal foot bath.

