1.*Wuqinxi* qigong will be exercised when participants who fail to fall asleep half an hour after going to bed, and cannot fall asleep again half an hour after waking up early. *Wuqinxi* consists of 5 parts: Tiger Exercise, Ape Exercise, Bear Exercise, Crane Exercise, and Deer Exercise. Exercise recommendation is based on the 5 elements theory of traditional Chinese medicine. According to the 5 elements theory, Tiger Exercise corresponds to anger, so practicing Tiger Exercise can ease the anger mood. Similarly, Ape Exercise corresponds to joy, Bear Exercise corresponds to thinking, Crane Exercise corresponds to sadness, and Deer Exercise corresponds to panic. Therefore, for participants who are unable to fall asleep due to irritability or anger, he or she will be suggested to get out of bed to practice Tiger Exercise. For participants who are unable to fall asleep due to joy, he or she will be suggested to get out of bed to practice Ape Exercise. For participants who are unable to fall asleep due to worries, they will be recommended to get up to practice Bear Exercise. For participants who are unable to fall asleep due to sadness, he or she will be required to get out of bed to practice Crane Exercise. For participants who are unable to fall asleep due to panic, he or she will be required to get out of bed to practice Deer Exercise.^[56]^2.Participants who have difficulty cooperating with sleep restriction at night (postponing bedtime) will be prescribed Chinese medicine foot bath by an attending physician dialectically based on the TCM theory, with no uniform limitations. The time of the Chinese medicine foot bath will be half an hour before bedtime at night as recommended by the physicians.3.Participants who feel tired during the day and have difficulty cooperating with the implementation of daytime sleep restriction will be given Chinese massage, with no specific restrictions on the duration, acupoints, and techniques of the massage. The therapist will implement the Chinese massage according to the specific conditions of the participants.

Participants in the control group will be given standard treatment based on BBT-I combined with oral trazodone medication (25–150 mg trazodone as an adjuvant therapy, 30 minutes before going to bed). Trazodone is selected because it is one of the most common drug prescriptions for insomnia in clinical practice.^[57–60]^ If the patient refuses to take trazodone, we will provide BBT-I only and record it.

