### Concomitant care

2.9

Participants who have been taking hypnotic drugs or antidepressants before enrollment will be permitted to continue taking them; however, the addition of hypnotic drugs or treatment other than the given interventions during trial will be prohibited if the participants did not take them before enrollment.

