Analysis of therapeutic efficacy within and between groups, and adherence analysis between the groups: the measurement data will be presented as the mean ± standard deviation, and the statistical inference will be performed using the *t*-test and rank-sum test. The count data will be presented as frequency (composition ratio), and Chi-Squared analysis or nonparametric analysis will be performed for exact probability or statistical inference, respectively. Sensitivity analyses will be used to assess the impact of missing outcomes, which include worst case assumptions and/or multiple imputation methods. Subgroup analysis will be used to analyze the main outcome and adherence according to associated medication (Trazodone used or not) and education level of the research subjects. SPSS 21.0 software (IBM, Armonk, NY) will be used for statistical analysis, which will adopt two-sided tests. *P* ≤ .05 will be considered to indicate statistically significant differences in the test.

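### The planned subgroup by trazodone use is set by allocation and a later open-label choice, so neither stratum gives a randomised comparison

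*Protocol article*

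**What the plan says.** The subgroup sentence in Section 2.10.2 (Data analysis) reads: "Subgroup analysis will be used to analyze the main outcome and adherence according to associated medication (Trazodone used or not) and education level". It does not tie trazodone use to baseline, and it does not limit the analysis to description or to one arm. The same paragraph sets two-sided testing with significance at P ≤ .05.

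Who takes trazodone is settled elsewhere:

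- Control arm (Section 2.7, Interventions): "Participants in the control group will be given standard treatment based on BBT-I combined with oral trazodone medication". Refusal is foreseen: "If the patient refuses to take trazodone, we will provide BBT-I only and record it".
- Experimental arm (Section 2.7): "TCMET include *Wuqinxi* qigong exercise, Chinese medicine massage, and herbal foot bath". Trazodone is not among these.
- Knowledge of allocation (Section 2.6, Randomization): "The study grouping will be revealed at the same time to both the patient and researchers".
- Other drugs (Section 2.9, Concomitant care): prior hypnotics and antidepressants may be continued. A conditional ban covers the rest: "the addition of hypnotic drugs or treatment other than the given interventions during trial will be prohibited". It applies only to those not already on such a drug or treatment at entry.

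**The concern.** A subgroup analysis asks whether the treatment effect differs between kinds of patient. The factor must be fixed before randomisation, so that each stratum still holds two randomly formed groups. Trazodone use fails this. In the control arm it follows from allocation plus acceptance or refusal once allocation is known. In the experimental arm it is absent by design, apart from any prior users.

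The risk lies in how the non-user result would read. It has the look of the traditional Chinese medicine external treatment (TCMET) plus brief behavioral therapy (BBT-I) compared with BBT-I alone, a comparison the design does not contain. It would in fact mix any treatment effect with whatever distinguishes people who refuse an assigned drug. Adherence is one of the two outcomes analysed this way, and willingness to take an assigned treatment is plausibly related to it. The Discussion acknowledges that some patients reject Western medicines, so some refusal is to be expected.

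**Working it through.** **Background figures.** Section 2.10.3 gives a difference of 2.5 ISI points, SD 4.1, two-sided α 0.05 and power 80%. The normal formula n = 2(1.960 + 0.842)² × (4.1/2.5)² gives 42.2, so 43 per arm. The t-test version gives 43.2, so 44 per arm and 88 in total, as stated. Then 88 × 1.1 = 96.8, which the protocol takes to 98, or 49 per arm. These figures are not in dispute; they supply the SD and the arm size used below.

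**Step 1: who falls in each stratum.** The refusal rate is not given, so a range is assumed. Prior trazodone users in the experimental arm are set to zero. With refusal rate r, control refusers ≈ 49r and control users ≈ 49 − 49r. Agreement between arm and trazodone use = (control users + 49)/98.

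| Assumed refusal | Users: experimental / control | Non-users: experimental / control | Agreement with arm |
|---|---|---|---|
| 0% | 0 / 49 | 49 / 0 | 100% |
| 10% | 0 / 44 | 49 / 5 | 95% |
| 20% | 0 / 39 | 49 / 10 | 90% |
| 30% | 0 / 34 | 49 / 15 | 85% |
| 50% | 0 / 25 | 49 / 24 | 76% |

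The user stratum has no between-arm contrast at any rate. The non-user stratum has one only because some controls refused.

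**Step 2: possible bias in the non-user stratum.** Suppose treatment has no effect, a fraction p of patients in both arms would refuse trazodone if offered it, and these patients score 0.5 SD worse (assumed). Take the other patients as zero.

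- Experimental mean: −0.5p, because would-be refusers stay in that group.
- Control refusers' mean: −0.5.
- False difference: −0.5p − (−0.5) = 0.5(1 − p).

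| p | False difference (SD) | ISI points (× 4.1) | Rejection rate of a nominal 5% test (simulated) |
|---|---|---|---|
| 10% | 0.45 | 1.8 | about 15–16% |
| 20% | 0.40 | 1.6 | about 19% |
| 30% | 0.35 | 1.4 | about 20% |

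If refusers score 0.5 SD better instead, the sizes are the same and the sign reverses, to the disadvantage of TCMET.

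**Step 3: precision of the same contrast.** Take SE = 4.1 × √(1/49 + 1/m), with m control refusers, and power ≈ Φ(2.5/SE − 1.96).

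- m = 5: SE 1.92, power 25%.
- m = 10: SE 1.42, power 42%.
- m = 15: SE 1.21, power 54%.

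Even without bias, the contrast would be weak against the planned 80%.

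**The case against.** **The sentence may mean something else.** It does not say that arms will be compared within each stratum. The authors may intend only to set acceptors against refusers within the control arm, and an analysis plan not shown may define it. This has some force: the wording is open. But the within-control contrast is not randomised either, and nothing in the text restricts the split to that use or to baseline medication.

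**The user stratum may not be empty.** The ban in Section 2.9 is conditional, and antidepressants taken before enrollment may continue. Section 2.2 excludes some antidepressant classes without saying whether trazodone belongs to one. A few experimental participants on trazodone are therefore possible, so few or none is the supportable statement. They would not restore a randomised comparison, because use in the control arm would still depend on allocation and later choice.

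**The size is assumed.** Neither the refusal rate nor the 0.5 SD comes from the protocol. Rejecting Western drugs does not imply poor behavioral adherence, and refusers could do better. A reader might infer that a positive non-user result would be spurious evidence for TCMET. The documents support only that it could be biased, in either direction.

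**Motive.** A reader might also infer that the trial is really after TCMET against BBT-I alone. Section 1.2 states the objective as a comparison with trazodone plus BBT-I, and Section 1.1 explains why behavior therapy alone was not chosen as comparator.

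**The trial is exploratory.** Section 1.3 says so, and this lowers the stakes. It does not make either stratum interpretable.

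**Conclusion.** The point holds for this one subgroup. As written, the plan splits on a variable determined by arm and by choice after allocation is revealed. One stratum has few or no experimental participants, and the other compares the experimental arm with self-selected control refusers. That conclusion does not depend on the refusal rate.

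The illustrative bias of 0.35 to 0.45 SD does depend on the assumed 10% to 30% refusal and the assumed 0.5 SD difference, and its direction is unknown.

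It would be wrong to read this as undermining the trial's main result. The comparison of all randomised participants and the sample size are untouched, and nothing says refusers leave their randomised arm in the main analysis. Education level, in the same sentence, is a baseline factor and raises no such problem. This should be fixed, but it concerns one subgroup analysis in an exploratory trial.

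**What to change.** In Section 2.10.2:

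1. Remove trazodone use as an inferential subgroup and keep education level.
2. State that control participants who refuse trazodone are analysed in the control arm as randomised.
3. Report the number of refusers and their outcomes descriptively, labelled as non-randomised.
4. If a medication subgroup is wanted, define it by psychotropic or hypnotic use before randomisation and test it with a treatment-by-factor interaction. Sections 2.2 and 2.9 imply that screening already asks about such use, but it is not named as an analysis variable, so confirm that it is recorded before randomisation.

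A complier-average analysis with allocation as the instrument should not replace the split. Allocation also changes exposure to TCMET, so it does not act on outcome through trazodone alone.

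The cost is a change to one sentence plus a short statement on refusers. Refusal is already to be recorded. The small downside is the loss of a planned exploratory split.

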#### Sample size calculation

2.10.3

The main observation index of this study is the ISI, and the sample size is calculated based on the two independent sample *t*-test. The sample size adjustment is based on the pool variance.^[63]^ According to our previous reports,^[25,50]^ the mean effect size of the control group is 8.4. A mean effect size difference (δ) of an increase in 2.5 for the experimental group relative to the control group will be considered effective. The overall sample standard deviation of ISI in the previous study was 4.1.^[49]^ Assuming that the variances of the 2 groups are similar, in a two-sided test with α at .05, sample size ratio of the 2 groups at 1:1, the test power (1 − β) at 80%, the sample size is calculated to be 88. We anticipate 10% loss to follow-up or drop-off rate. Thus, t total sample size is calculated as 96.8, which is approximately 98 people, including 49 people in each of the 2 groups.

## Composition and responsibilities of the coordinating center

3

This study is a multicenter study that will be designed, performed, and coordinated in Jiangsu Vocational College of Medicine, Community Health Service Center of Dongting Lake Street and the Community Health Service Center of Xindu Street. The study team will meet weekly. The trial is supported by:

1.Monitoring group: supervises the trial, audits data, takes medical responsibility for the participants, provides BBT-I, and trains the follow-up group.2.Physician group: identifies potential recruits, acquires informed consent, provides medical treatment according to the study protocol.3.Follow-up group: conducts follow-up by telephone and records data in the NCDFP, feeds back questions to the Physician group, and safeguards data.4.Supportive group: performs trial registration, safety reports, and coordinates with each team.

## Discussion

4

In the design of this study, we fully considered the limitations of the professional ability of physicians in the Chinese community, the limitations of the examination methods in the primary medical institutions, the limitations of sleep-related drug administration by the community physicians, the higher acceptance of some TCM non-pharmaceutical therapies among the patients, and problems such as rejection of Western medicines (e.g., sleeping pills) among Chinese patients. This study will explore the integration of TCMET, drugs, and regular follow-up care on BBT-I to improve behavioral therapy adherence in participants with insomnia, thereby achieving curative effects. The results of this study will provide clinical evidence for the implementation of CBT-I in primary healthcare institutions in China.

The innovations of this study are:

1.The research design, which fully considers the various real-world constraints of primary medical institutions in China.2.The research, which adopts active telephone follow-up design for each behavioral therapy step to achieve better behavioral therapy adherence through reminding and supervising the participants.3.Comparative analysis of the follow-up of behavioral therapy adherence and sleep diary, which determines the reliability and validity of the BBT-I adherence questionnaire to explore the effectiveness of the questionnaire in evaluating participants’ behavioral therapy adherence.4.Accurate integration between *Wuqinxi* qigong exercise, Chinese massage, herbal foot bath, and behavioral treatment.5.The dosage of trazodone used in the control group at 25 to 150 mg/day instead of a fixed drug/fixed dosage design.

Due to the high prevalence, morbidity, and social cost of insomnia, this study may generate new information that can have a direct impact on the model of promoting CBT-I for insomnia, benefiting insomnia patients and the society, especially for patients who live in regions with weak healthcare systems.

## Experimental status

5

This clinical study is currently in the active recruitment phase. As of April 17, 2021, patient recruitment has been initiated and 25 subjects have been enrolled. This is protocol version number 2, January 30, 2021.

## Declarations

6

### Ethics approval and safety monitoring

6.1

The research protocol has been approved by the Chinese Ethics Committee of Registering Clinical Trials (ethical review number: ChiECRCT20200452) and has been filed at the corresponding community health service center.

The trial will be monitored by the Steering Committee and the Data and Safety Monitoring Board (DSMB). The DSMB comprises 3 independent researchers, 1 network data security expert, 1 psychiatrist, and 2 members of the follow-up group. The DSMB will be responsible for monitoring participant safety and data quality, and will have access to those interim results and make the final decision to terminate the trial.

Adverse events will be recorded during follow-up. In the event that participants report severe symptoms of depression, anxiety, or previously undiagnosed severe psychiatric conditions to follow-up staff, the staff will inform their clinical team and will recommend the patient to a higher-level hospital to psychiatry or clinical psychology if necessary. Serious harm is expected to be impossible. However, if harm does occur, the medical liability insurance will cover care for participants.

As a funding limitation, there is no independent audit. The Science and Technology Department and Audit Office of Jiangsu Vocational College of Medicine are responsible for performing audit work once a year.

In the event that any substantial modifications to the protocol occur, both the Chinese Ethics Committee of Registering Clinical Trials and participants will be notified. If necessary, additional consent will be requested and registered. Non-substantial amendments will be recorded and filed.

### Confidentiality

6.2

Unique study numbers will be used to label the participants for the research data. The only dataset with participant identifier information is the NCDFP, which is used to follow-up and contact participants. The login ID and password will only be provided to the research team during the study period. The storage server system of the NCDFP is installed in the Jiangsu Vocational College of Medicine and is not publicly available. After the completion of the study, the main researchers will submit the paper-based original files and data to the Science and Technology Department of the College for preservation, and the medical records will be kept in the corresponding hospitals. Patient identity details will not be reported in the publication.
